#### Randomization

2.3.4

The participants will be randomized to the Optimized-tDCS and Sham-tDCS groups using a 1:1 ratio following the order of registration by a statistician who will not be involved in the application of the clinical trial. A stratified blocked randomization method with prespecified block sizes will be used. The stratification factor will be the hospital from which participants will be recruited. Random allocation numbers will be sealed in an opaque envelope and delivered to the medical device investigator who will administer the tDCS device in the hospital and will not be involved during the outcome measurement periods or other periods of the research.

### Intervention

2.4

#### Transcranial direct current stimulation

2.4.1

The tDCS device that will be used during the intervention period is a portable, battery-driven device called NEUROPHET innk (Neurophet, Seoul, Republic of Korea). The device can deliver a weak direct current between 1 and 2 mA for a programmed period through sponge-coated electrodes. In this study, participants will receive a stimulus of 2 mA for 30 min through two paired (one anode, one cathode) disk electrodes *R* = 1.5 cm.

The device is programmed to follow a ramping protocol: ramping up the current in 30 s to reduce discomfort at the beginning of the intervention and ramping down in 30 s at the end. Additionally, the device can continuously monitor the impedance values on the patient’s skin in real time. The stimulation is automatically terminated, and the medical device investigator verifies the patient’s condition and skin if an impedance of more than 13 Kohm is detected.

#### Individualized 3D brain modeling

2.4.2

NEUROPHET tES LAB software (version 3.0; Neurophet, Seoul, Republic of Korea) will be used for brain modeling, calculate the tDCS-induced E-field and determine each participant’s optimal electrode location (according to individual brain structural characteristics) to stimulate a specific target area. In a recent simulation study, the optimized tDCS electrode position yielded a significant 55.28% increase in the E-field over the left dorsolateral prefrontal cortex (DLPFC) compared with the conventional 10–20 EEG-based system location (26). This emphasizes the potential of simulation software to enhance stimulation by optimizing the electrode locations in individual brain structures.

For the creation of the brain model and later analysis of the tDCS-induced E-field, all participants will undergo a T1-weighted MR image at baseline. The software will analyze and segment T1-weighted MR images and reconstruct a 3D model of the participant’s brain, including the following structures: skin, skull, cerebral gray and white matter, cerebellum gray and white matter, CSF, and ventricles. The electrical conductivity of the tissues is pre-programmed as follows: skin, 0.465 S/m; skull, 0.010 S/m; cerebral and cerebellar gray matter, 0.276 S/m; cerebral and cerebellar white matter, 0.126 S/m; and CSF and ventricle 1.65 S/m (27). Following the creation of the brain model, an investigator will assign landmarks (nasion, inion, and both preauricular points) to the model to assign the tDCS electrodes location.

#### Optimized-tDCS group

2.4.3

For the optimized-tDCS group, guided by the 10–20 EEG-based system, the structure that represents the DLPFC will be selected on the brain model of each participant, as the DLPFC (F3) area is known for its direct relationship with MCI (28). Subsequently, a 3D model representation of an anode electrode will be located above the selected target, while a 3D model representation of the cathode electrode will be located over the contralateral supraorbital zone (Fp2), both electrodes will be disk type, *R*: 1.5 cm. Next, the tDCS intensity (2 mA) to be used in the study will be input into the software.

Based on these initial locations, tDCS parameters, and the conductivity of the brain tissues, the software analyzes the optimal electrode position for each participant. The F3 and Fp2 positions are used as references, as the software will “move” the electrodes around the target area to determine the location (according to the participant’s brain characteristics) that generates the maximum E-field-induced by tDCS. Finally, the software will provide the necessary guides to find the optimized electrode position on the participant’s head.

Figures 2, 3 show visual representations of the NEUROPHET tES LAB program and the process to determine the optimized electrode locations. Figure 4 shows how the program offers the necessary guides to find the personalized electrode position on the participant’s head.

**Figure 2 fig2:**
[figure not shown]
3D Brain model creation and landmarks 1. T1-weighted MR image of a participant (head model example) and segmentation results based on tissue electrical conductivity; 2. 3D brain model anterior view: landmark locations; 3. 3D brain model posterior view: landmark locations; 4. Individualized selection of tDCS electrode positions (F3 – Fp2). RPA, right pre-articular; LPA, left pre-articular.

**Figure 3 fig3:**
[figure not shown]
Comparison between 10–20 EEG system-based electrode location E-field and Optimized electrode location E-field. Head model example. Conventional tDCS 10–20 EEG system-based electrode position: (1.1) 10–20 EEG system-based electrode map. (2.1) Common electrode locations: F3 (anode, red) and Fp2 (cathode, gray). (3.1) Calculation of the E-field generated according to stimulation parameters. The E-field magnitude in the target zone (F3) was: 0.20 V/m. Optimized Active tDCS electrode position: (1.2) The target area is input into the program (F3), and the electrodes were initially located over the same locations as in conventional tDCS. (2.2) Based on the stimulation parameters, the program estimates the best electrode position to create the highest E-field magnitude on the target area. (3.2) After the calculations, the program shows the new personalized electrode position. (4.2) E-field magnitude generated according to the stimulation parameters and the optimized electrode position, E-field magnitude at the target zone (F3): 0.40 V/m.

**Figure 4 fig4:**
[figure not shown]
Personalized Optimized electrode position finding guide (example). 1. Anode location (F3); 2. Cathode location (Fp2). RPA, right pre-articular; LPA, left pre-articular.

#### Sham-tDCS group

2.4.4

In the case of the Sham-tDCS group, as the optimized-tDCS group, the software will provide each participant’s optimized tDCS electrodes position and the guides for the localization of the positions on the participant’s head. No stimulation will be performed. The device is going to ramp-up in 30 s and automatically ramp-down in another 30 s at the beginning and end of the stimulation to provide the initial sensation of tDCS.

### Blinding

2.5

The participants and investigators in charge of performing the outcome measurements will remain unaware of the group allocation until the end of the study, and the data has been fully analyzed.

Owing to the nature of the study and individualized tDCS electrode localization, it is necessary that one investigator per hospital, in this case, the investigational device manager, remains unblinded during the investigation. The investigational device manager will be in charge of applying tDCS during the clinical trial; however, it will not be present during any outcome measurement period or at any other stage of the trial.

### Outcome measurements

2.6

Outcome measurements will be obtained at three points: baseline (on the screening day), First Post-test (after the last session of the first set), and Second Post-test (after the last session of the second set) by investigators blinded to the participants’ allocation.

#### Primary outcomes

2.6.1

##### Alzheimer’s disease assessment scale-cognitive subscale

2.6.1.1

ADAS-Cog is considered the gold standard tool for assessing the effectiveness of anti-dementia treatment. It is frequently used in many observational and experimental studies, particularly in studies with patients ranging from those with normal cognition to MCI looking for treatments, to slow or stop the progression of the disease before it develops into severe neuropathology and dysfunction (29). The scale includes 11 tasks that include both participant-completed tests and observer-based assessments. Together, these tasks assess the cognitive domains of memory, language, and praxis. The specific tasks include word recall, naming objects and fingers, commands, constructional praxis, ideational praxis, orientation, word Recognition, and language. The total ADAS-Cog score ranges from 0 to 70, with higher scores indicating greater impairment (29). In this study, a validated Korean version of the test will be used (30).

##### Korean version of mini-mental state examination

2.6.1.2

The K-MMSE is a Korean-validated version of the MMSE, which is a measurement tool designed for the quantitative estimation of CI severity and documentation of cognitive changes. It can be administered in 5–10 min, with questions grouped into seven categories, each representing a different cognitive domain or function: orientation to time, orientation to place, registration of three words, attention and calculation, recall of three words, language and visual construction. Scores range from 0 to 30, with lower scores indicating greater impairment (31, 32).

#### Secondary outcomes

2.6.2

##### Korean version of Montreal cognitive assessment

2.6.2.1

The MoCA-K is a Korean-validated version of the MoCA that is employed to assess and identify MCI. It can be administered in approximately 10 min. The MoCA-K assesses 11 domains, including attention and concentration, executive functions, memory, language, visuoconstructional skills, conceptual thinking, calculation, and orientation. The highest achievable score is 30 points, with lower scores indicating a greater CI (33, 34).

##### Hamilton depression rating scale

2.6.2.2

HAM-D is a commonly used scale for assessing depression. Seventeen items are used to assess the severity of depressive symptoms: depressed mood, feelings of guilt, suicide, early insomnia, middle insomnia, late insomnia, work and activities, psychomotor retardation, psychomotor agitation, anxiety (psychic), anxiety (somatic), somatic gastrointestinal, somatic general, genital symptoms, hypochondriasis, weight loss, and insight. The overall score ranges from 0 to 52 points, with higher scores indicating more severe depression (35, 36).

##### Seoul-instrumental activities of daily living

2.6.2.3

The S-IADL scale is designed to assess an individual’s capacity to perform instrumental and social activities of daily living. These include the ability to prepare balanced meals, remember appointments, keep financial records, and remember to take medications. It comprises 15 items with possible scores ranging from 0 to 45. Lower scores indicated better functioning (37).

##### Imagining analysis

2.6.2.4

MR examinations for efficacy evaluation include 3D T1 MRI, resting-state functional MRI, and diffusion weighted image (DWI). The examinations will be performed at baseline and 8 weeks after tDCS application, and could be performed at screening instead of baseline or if results are available within 1 year of the consent date. 3D T1 MR scans will be acquired within a voxel size of 1 × 1 × 1 mm^3^, fMRI will be acquired at a resting state to analyze changes in neuronal efficiency, and diffusion tensor imaging (DTI) will be used to assess neural network connectivity.

### Sample size

2.7

A prospective sample calculation was not performed because the current study protocol is for assessing feasibility, safety, and trends in effectiveness, which will be utilized to generate data for future full-scale randomized controlled trials. However, as sample sizes of a minimum of 24 participants (12 per group) were recommended, we decided to recruit a minimum of 32 participants based on the predicted recruitment rates within the study timeframe (38, 39). Considering a 20% dropout rate, the projected number of participants to be recruited will be 40.

### Statistical analyses

2.8

Descriptive statistics (average, standard deviation, median, minimum, and maximum) will be represented for each group for the changes found from baseline to the first and second post-tests. The Least Squares Mean (LSM) with a 95% confidence interval will be used to determine the trend of changes within time per group. The Shapiro–Wilk test will be used to determine data normality. If normality is met, the paired *t*-test will be used for within-group analysis at each time point; if normality is not met the Wil-coxon sign rank test will be performed. Following this, an independent *t*-test will be used for between-group analysis; if normality is not met, a Wilcoxon sign rank test would be performed. Additionally, an analysis of covariance (ANCOVA) with baseline as a covariate will be performed for a group × time analysis.

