Therefore, an accessible software capable of performing brain structure segmentation based on MRI to calculate the E-field induced by tDCS was developed to facilitate the maximal stimulation effect based on individual unique brain characteristics (24). This software has been used previously in research and is expected to facilitate the use of optimized tDCS in clinical settings in the near future (25).

Considering all the above-mentioned studies, the present feasibility randomized double-blind controlled trial study protocol aims to outline the study methods and resources required to determine the feasibility and safety of a treatment for patients with MCI induced by AD with personalized optimized tDCS for the future design of a full-powered trial. The specific aims are to (1) determine the feasibility of optimized tDCS in the treatment of patients with MCI induced by AD for the improvement of cognitive function compared to a sham group, (2) determine the safety of using optimized tDCS in patients with MCI induced by AD, and (3) obtain valid data to sustain the calculation of a sample size for a fully powered trial, should tendencies of efficacy be present.

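### A Shapiro–Wilk result selects a mean-based or rank-based between-group test, and the baseline-adjusted ANCOVA that does not depend on it is not named as the main analysis

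*Protocol article*

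**What the plan says.** Section 2.8 (Statistical analyses) of the protocol article sets out this sequence.

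- Descriptive statistics are given per group "for the changes found from baseline to the first and second post-tests", and least squares means with 95% confidence intervals are given per group over time. Neither is conditional on normality.
- "The Shapiro–Wilk test will be used to determine data normality". The section gives no significance level for this test. It does not say whether the test is applied to raw scores, changes or residuals, or by arm or pooled.
- Within groups, a paired t-test "will be used for within-group analysis at each time point", with a signed-rank test as the alternative.
- Between groups, an independent t-test "will be used for between-group analysis"; "if normality is not met, a Wilcoxon sign rank test would be performed".
- Finally: "Additionally, an analysis of covariance (ANCOVA) with baseline as a covariate will be performed for a group × time analysis".

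The section does not say which between-group result is the main one: the t-test, the rank test or the ANCOVA. There are two primary scales, ADAS-Cog (0 to 70) and K-MMSE. For K-MMSE, section 2.6.1.2 states: "Scores range from 0 to 30, with lower scores indicating greater impairment". Inclusion criterion 3 requires a K-MMSE of at least 23.

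**The concern.** The choice between a comparison of means and a comparison of ranks is made by a preliminary test on the trial data. In arms of this size that preliminary test is a poor guide. K-MMSE entry values lie between 23 and 30, so changes are likely to take few distinct whole-number values. Shapiro–Wilk can then reject because of rounding and ties, even when the underlying change is normal and a t-test or ANCOVA would be sound.

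Nothing in section 2.8 holds the choice constant across visits or scales. One scale could therefore be judged on means at the first post-test and on ranks at the second, and the two primary scales could be judged on different contrasts. When a result is borderline, the branch taken can change the conclusion. Neither branch adjusts for baseline as a covariate. If the gated test is read as the headline, the reader gets the less suitable of two analyses that are both already planned.

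This is separate from the naming of the fallback. A signed-rank test is a paired or one-sample test and does not fit two independent arms, but replacing it with a rank-sum test would leave the gate in place.

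**Working it through.** **Inputs from the protocol article.** Allocation 1:1 (section 2.3.4). Minimum 32 participants, 20% dropout, 40 to be recruited (section 2.7). Two post-tests (section 2.8).

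The stated recruitment figure reproduces: 32 / (1 − 0.20) = 40. The arms therefore hold 32/2 = 16 to 40/2 = 20 participants.

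**Assumptions, because the article gives no values.** Gate level 0.05. Gate applied per scale, visit and arm, with rejection in either arm switching to ranks. Change truly normal and then rounded to whole numbers. SDs as listed. A two-sample rank-sum test stands in for the misnamed fallback.

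**Step 1: how often the gate rejects in one arm.** Simulated Shapiro–Wilk rejection rate p for rounded normal change (5,000 runs each). For exactly normal continuous data, p = 0.05 by definition.

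**Step 2: chance of switching at one visit.** q = 1 − (1 − p)².

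**Step 3: chance that the two visits take different branches, treating visits as independent.** D = 2q(1 − q).

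| Change | p (n = 16 / 20) | q | D |
|---|---|---|---|
| Continuous normal | 0.050 | 0.098 | 18% |
| Integer, SD 4 | 0.061 / 0.070 | 0.118 / 0.135 | 21% / 23% |
| Integer, SD 2 | 0.134 / 0.148 | 0.250 / 0.274 | 38% / 40% |
| Integer, SD 1.5 | 0.242 / 0.285 | 0.425 / 0.489 | 49% / 50% |
| Integer, SD 1 | 0.619 / 0.689 | 0.855 / 0.903 | 25% / 17% |

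For example, at SD 2 and n = 16: q = 1 − 0.866² = 0.250, and D = 2 × 0.250 × 0.750 = 0.375.

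D cannot exceed 50%, and SD 1.5 sits close to that ceiling. At SD 1 it falls again, because both visits usually go to ranks.

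**Step 4: does the independence assumption drive this?** A separate simulation with latent correlation 0.6 between visits and no group difference (3,000 runs per scenario) gave, at 16 / 20 per arm:

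- continuous normal: 18% / 18%
- SD 4: 22% / 23%
- SD 2: 38% / 39%
- SD 1.5: 48% / 51%
- mildly skewed integer change: 45% / 39%
- score capped at 30: 40% / 46%

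SD 1 was not run in this version. The other figures agree with step 3.

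**Step 5: error rate.** In the same null runs, type I error was 4.6–5.6% with the gate, 4.4–5.5% with a t-test always and 4.1–5.1% with a rank-sum test always.

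**Step 6: does the branch matter to the conclusion?** The t-test and the rank-sum test fell on opposite sides of p = 0.05 in 1.5–2.5% of null runs. With an assumed effect of 0.7 SD and 16 per arm, they did so in 6.5% of runs (integer change, SD 2) and 9.6% (skewed integer change).

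**The case against.** **ANCOVA is run whatever the gate says, and an article may leave the choice of main model to the full protocol or SAP.** The first part is true and makes the fix small. But the article does not merely stay silent: it writes out a data-dependent rule for the between-group comparison and places the ANCOVA after it as an addition. That rule is open to comment as it stands.

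**The by-visit gate is a reading, not the literal text.** This stands. The wording about each time point is attached only to the within-group test, and nothing says that both arms must pass. Applying the gate by scale and visit is the natural reading, since the section deals with changes to both post-tests, but every switching probability above depends on it.

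**Stronger conclusions that a reader might draw, and that the documents do not support:**

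- *The gate inflates false positives.* It does not to any material extent (step 5).
- *The rank branch deprives the third aim, to "obtain valid data to sustain the calculation of a sample size for a fully powered trial", of its inputs.* It does not. Means and SDs of change and per-group least squares means with 95% CI are reported on either branch, and so is the ANCOVA. The same summaries allow the two visits to be compared.
- *The analysis is not pre-specified.* The branching rule is written in advance. The fair complaint is that its outcome depends on the data.
- *A trial decision hangs on the gated p-value.* Section 2.7 describes a study of feasibility, safety and trends without a sample size calculation, and the article states no success rule tied to this test.
- *Both primary scales are heavily affected.* At SD 4, used here to represent a wider scale such as ADAS-Cog, switching is only a little above the rate for continuous data.

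**Conclusion.** The point holds as one of consistency and clarity. Section 2.8 lets a normality test on about 16 to 20 observations per arm pick the between-group contrast, and it leaves the analysis that avoids this problem without main status. Under the assumptions listed, the chance of a different type of test at the two post-tests of one scale runs from about 17% to 51%. It depends strongly on an SD of change that the article does not give. The choice of test would alter a p < 0.05 conclusion in roughly 6.5–9.6% of runs under the assumed 0.7 SD effect.

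Because this is a feasibility study with no powered comparison, error rates are preserved and the descriptive inputs for the next trial survive, the matter is of moderate weight. It should be corrected, but it does not threaten the trial.

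**What to change.** In section 2.8 and the analysis plan:

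1. Delete the Shapiro–Wilk gate for the between-group comparison.
2. Name the already planned baseline-adjusted ANCOVA difference between arms, with its 95% CI, as the main between-group analysis for every scale at both post-tests, whatever the normality result.
3. Report a two-sample rank-sum test of change only as a labelled sensitivity analysis.

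With one analysis fixed in advance, the chance of a different method at the two visits is zero by construction.

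The cost is a change of wording, with no extra participants or data. The downside is some loss of efficiency if a scale proves strongly skewed, which the sensitivity analysis would show.

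### The fallback test for the between-group comparison is a paired test (Wilcoxon signed-rank), which does not fit two independently randomised arms

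*Protocol article*

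**What the plan says.** Section 2.8 sets out the tests in order.

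- **Normality check:** "The Shapiro–Wilk test will be used to determine data normality".
- **Within-group change:** a paired t-test at each time point, and "if normality is not met the Wil-coxon sign rank test will be performed".
- **Between-group comparison:** an independent t-test "will be used for between-group analysis; if normality is not met, a Wilcoxon sign rank test would be performed".
- **Covariate-adjusted analysis:** "Additionally, an analysis of covariance (ANCOVA) with baseline as a covariate will be performed for a group × time analysis".

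On the design, section 2.3.4 (Randomization) states: "The participants will be randomized to the Optimized-tDCS and Sham-tDCS groups using a 1:1 ratio". Allocation is blocked and stratified by hospital; no participant is matched to another. Section 2.7 (Sample size) sets a minimum of 32 participants and a recruitment target of 40, allowing for 20% dropout. The article nowhere names a rank-sum or Mann-Whitney test.

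**The concern.** The signed-rank test ranks the absolute values of paired differences and uses their signs. It suits within-group change, because each participant supplies both values. Between arms, the observations come from different people and there is no rule for deciding which optimized participant is subtracted from which sham participant.

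The article is not silent here, so this is not a detail left to the full analysis plan: it names a specific test that does not fit the design. An analyst who reaches this branch cannot follow the text and must choose a replacement after seeing the data, which defeats the purpose of prespecifying. The branch applies to both primary outcomes (ADAS-Cog and K-MMSE) and to the secondary scales. The comparison with sham is part of the first specific aim, and the third aim is to supply data for sizing a full trial.

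**Working it through.** **Inputs from the article.** Two unmatched arms, 1:1 (section 2.3.4). Minimum 32 participants, 20% dropout, 40 to recruit (section 2.7). Between-group fallback: signed-rank (section 2.8).

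**Assumptions not in the article.** Exactly 20 randomised per arm; participants drop out independently, with the same probability in both arms; completers are analysed.

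**Step 1: the plan's own figure.** 32 / (1 − 0.20) = 40. It reproduces.

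**Step 2: which test fits which comparison.**

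| Comparison | Data structure | Test if normal | Fallback named | Fits? |
|---|---|---|---|---|
| Within group, over time | Paired (same person) | Paired t-test | Signed-rank | Yes |
| Optimized versus sham | Independent (different people) | Independent t-test | Signed-rank | No |

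**Step 3: how likely are unequal arms?** With d the dropout rate, the number of completers in each arm is Binomial(20, 1 − d). Then

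P(equal) = Σₖ [C(20, k) (1 − d)ᵏ d²⁰⁻ᵏ]², for k = 0 to 20.

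| Dropout d | P(equal) | P(unequal) |
|---|---|---|
| 5% | 0.31 | 0.69 |
| 10% | 0.21 | 0.79 |
| 20% (planned) | 0.158 | 0.842 |
| 30% | 0.14 | 0.86 |

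Unequal arms are the expected case over this whole range. A signed-rank test of 17 against 15 values stops with an array-shape error, since there are no 1-to-1 differences to form.

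**Step 4: what happens if the arms are equal?** One skewed data set was simulated with 16 per arm (shifted exponential values; illustrative, not trial data). The same values were paired at random 5,000 times. The signed-rank p-value ran from 0.009 to 0.53, with the central 95% of pairings between 0.039 and 0.32, and 4.7% of pairings gave p below 0.05. The rank-sum test gave a single value, p = 0.080. The exact range belongs to that data set; the dependence on pairing is general.

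**Step 5: chance of reaching the branch and being unable to run it.** If the trigger and the dropout are independent, this is P(trigger) × 0.842. The article does not give P(trigger), so the following only shows a range. Suppose Shapiro–Wilk is applied at 5% with 16 per arm, and its rejection rate in one arm is 0.22 or 0.42 (simulated for gamma(4) and gamma(2) skew).

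- Rejection in one tested arm is the trigger: 0.22 × 0.842 = 0.19; 0.42 × 0.842 = 0.35.
- Rejection in either arm is the trigger: (1 − 0.78²) × 0.842 = 0.33; (1 − 0.58²) × 0.842 = 0.56.
- Truly normal data, either arm: (1 − 0.95²) × 0.842 = 0.08.

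**Step 6: does the replacement work at this size?** In simulated skewed data with no difference between arms, the two-sided rank-sum test at nominal 0.05 rejected 0.050 of the time with 16 per arm and 0.048 with 20 per arm. It runs for any pair of arm sizes.

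**The case against.** The best reply is that this is a slip of naming. The fallback is attached to an independent t-test, so the independent-samples Wilcoxon test was very probably meant. With unequal arms the software would refuse to run, and the error would come to light. The study is also unpowered and looks for feasibility, safety and trends, so no confirmatory decision rests on this p-value. All of this is fair and limits the weight of the point. It does not remove it: nothing in the article corrects the name, and the correction should be made before the data are seen.

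Two stronger readings are tempting, and the article supports neither.

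- **That the primary contrast cannot be computed.** Only the non-normal branch is faulty. The independent t-test remains where normality is accepted. The ANCOVA carries no normality condition in the text and still gives a baseline-adjusted comparison. Section 2.8 does not label the t-test path as the primary analysis.
- **That the planned analysis fails 84% of the time.** That figure is the chance of unequal arms under assumed independent dropout. The branch must also be reached, and the article gives no distribution for any outcome. The scales are bounded, but section 2.8 summarises changes from baseline, which need not be skewed as raw scores may be.

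Using a Shapiro–Wilk pre-test at all is open to debate, but that is a separate choice and the point does not depend on it. The signed-rank fallback for within-group change is correct.

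**Conclusion.** The point holds in a limited form: section 2.8 assigns a paired test to a comparison of unpaired arms. If an outcome reaches that branch, the test as written either cannot be run or has no unique answer. That it cannot be run is the more likely of the two: about 84% at the planned dropout, and 69% to 86% for dropout between 5% and 30%, given 20 per arm and independent dropout. How often the branch is reached cannot be settled from the article; the joint figures of 8% to 56% rest on assumed distributions and an assumed trigger rule. That the test does not fit the design needs no assumption, as it follows from the text of sections 2.3.4 and 2.8. The effect is confined to the fallback, so this is a clear error with a simple correction and not a failure of the whole between-group analysis.

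**What to change.** In section 2.8 and the corresponding analysis plan text, replace the between-group fallback with the Wilcoxon rank-sum (Mann-Whitney) test, and state that the signed-rank test is for within-group change only.

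Optionally, name the baseline-adjusted ANCOVA already planned as the main between-group analysis for every outcome, with the rank-sum test in support. The main result would then not depend on the outcome of a normality pre-test.

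The cost is one sentence, or two with the option. The recruitment target of 40, the visits and the data collected do not change. The change should be dated and made before unblinding.

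### The only baseline-adjusted model is aimed at group × time, which does not estimate optimized versus sham; the adjusted group difference at each post-test should be the between-group estimate

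*Protocol article*

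**What the plan says.** - Section 2.6, Outcome measurements: "Outcome measurements will be obtained at three points". These are baseline and two post-tests on the same participants, which Table 1 places at V16 and V31.
- Section 2.8, Statistical analyses, after the within-group tests: "Following this, an independent *t*-test will be used for between-group analysis". No covariate is attached to this test. The least squares means with 95% intervals in the same section describe change over time within each group.
- The same section then adds that "an analysis of covariance (ANCOVA) with baseline as a covariate will be performed for a group × time analysis". It names no other covariate, no error structure, and no contrast as the treatment effect.
- Section 2.3.4, Randomization: "The stratification factor will be the hospital from which participants will be recruited". There are three hospitals.
- Section 2.7, Sample size: at least 32 participants, and 40 after allowing for dropout. No sample size calculation was made.

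**The concern.** The hypothesis in the Abstract and Discussion is that optimized tDCS improves cognition compared with sham. The baseline-adjusted model is the more precise between-group analysis in the plan, yet it is directed at a term that does not measure that comparison. A benefit present by V16 and held to V31 would leave the interaction null. The comparison that does address the hypothesis is left to an unadjusted test.

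The third specific aim in the Introduction is to supply data for sizing a full trial if signs of efficacy appear. What is at stake is therefore a misread group × time result, and a less precise effect estimate than the data could give when the next trial is planned.

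**Working it through.** **Inputs from the protocol.** Allocation is 1:1, and at least 32 participants means 16 per arm. The plan's own figure reproduces: 32 / (1 − 0.20) = 40. There are two post-tests, baseline as covariate, and three hospitals.

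**Assumptions not in the protocol.** Two-sided 5% tests; baseline-post correlation r = 0.6 to 0.8; correlation between post-tests p = 0.7 to 0.85; equal variance at the two post-tests.

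**1. What the interaction tests.** Let D16 and D31 be the baseline-adjusted group differences at the two post-tests. With baseline on the right-hand side, group × time is D31 − D16. If D16 = D31 = D, this is zero however large D is. Other readings of the sentence do not help:
- If baseline were also a level of time, it would be both covariate and response.
- If an ANCOVA were run at each visit, there would be no time term.
- A repeated-measures ANCOVA settles the correlation, but its interaction is still D31 − D16.

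Simulation with 16 per arm and a benefit of 0.6 SD at both visits:
- Correctly modelled interaction: rejects in about 4 to 6% of trials.
- Baseline-adjusted V31 contrast: rejects in about 53 to 77%.

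Check on the V31 contrast: the noncentrality is [0.6/√(1 − r²)] / √(2/16), which is 2.12 at r = 0.6 and 2.83 at r = 0.8. With 29 df the power is 0.54 and 0.78. This is slightly high because it ignores chance imbalance in baseline.

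A separate simulation, with a constant benefit of 0.8 residual SD and residual correlation 0.3 to 0.9, gave 0.048 to 0.055 for the interaction and 0.59 to 0.76 for the correctly modelled visit-averaged group effect.

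**2. Correlation between the post-tests, if the two rows were stacked as independent.** The residual correlation after baseline adjustment is q = (p − r²)/(1 − r²). In large samples, the false-positive rate is 2[1 − Φ(1.96/√(1 + q))] for the visit-averaged group effect and 2[1 − Φ(1.96/√(1 − q))] for the interaction.

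| r | p | q | Visit-averaged group effect | Interaction |
|---|---|---|---|---|
| 0.6 | 0.70 | 0.53 | 11.3% | 0.4% |
| 0.6 | 0.85 | 0.77 | 14.0% | <0.1% |
| 0.8 | 0.70 | 0.17 | 7.0% | 3.2% |
| 0.8 | 0.85 | 0.58 | 11.9% | 0.2% |

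Simulation agrees: about 7 to 14% and about 0 to 4%. The V31 contrast from the same stacked model stays at about 5 to 6%. Its variance depends on the single-visit residual variance, which stacking estimates correctly when the two visits have equal variance. Only the degrees of freedom are overstated: 64 − 5 = 59, against 32 − 3 = 29 for an ANCOVA at V31 alone.

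**3. Precision of the t-test.** If it is applied to change scores, the variance per observation is 2(1 − r)σ², against (1 − r²)σ² for ANCOVA. The ratio is (1 + r)/2, that is 0.80 at r = 0.6 and 0.90 at r = 0.8. Baseline adjustment is then worth 1/0.90 = 1.11 to 1/0.80 = 1.25 times the participants.

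**4. Hospital left out** (V31 ANCOVA, 16 per arm; power for a benefit of 0.8 residual SD; between-hospital SD assumed, in residual SD units).
- SD 0.5: type I error 0.036 without hospital and 0.052 with it; standard error 0.387 and 0.359; power 0.51 and 0.575.
- SD 0.3: power 0.54 and 0.56.
- SD 0: no loss.

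**The case against.** The strongest reply is that the ANCOVA is only additional. An independent t-test compares the arms directly, so a stable benefit could still show there, and nothing in section 2.8 makes the interaction p-value the efficacy test. This stands and limits the harm. It does not remove the point: the t-test is unadjusted, and where normality fails the section replaces it with a signed-rank test, which is a paired procedure.

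A reader might infer that the plan ignores the correlation between post-tests. The article does not say so. It gives no error structure, and a repeated-measures ANCOVA or an ANCOVA per visit is possible; such detail may sit in the full protocol or analysis plan. The 7 to 14% applies to one reading only, and to the visit-averaged effect only.

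A reader might also infer that leaving out hospital threatens validity. It does not. The covariate list may be completed elsewhere, and omission makes the test conservative.

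Finally, a valid t-test alongside a planned ANCOVA is not in itself an error, and no figure in the protocol is wrong. Both are accepted.

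**Conclusion.** The point holds, at moderate severity. As worded, the adjusted model is directed at whether the group difference changes between V16 and V31, and section 2.8 names no adjusted contrast as the treatment effect. Under a constant benefit, the interaction rejects no more often than chance. That conclusion follows from the form of the model and does not depend on the assumed correlations.

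The remaining parts are secondary and rest on assumptions. The precision gain over a change-score t-test needs r of 0.6 to 0.8. The inflated error rate needs the two rows to be treated as independent, which the text does not state. The hospital loss needs hospitals to differ.

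The documents do not support the stronger conclusion that the efficacy analysis is invalid or that a real benefit would go undetected. The trial is an unpowered feasibility study with a direct group comparison also planned. The cost is a misleading secondary result and less precise estimates for the next trial.

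**What to change.** For each scale, make the optimized-minus-sham difference, adjusted for baseline and hospital and given with its 95% CI at each post-test, the between-group estimate, with V31 leading.

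Obtain it from one repeated-measures model of the V16 and V31 scores, with group, visit, group × visit, baseline and hospital as fixed effects and a stated within-person covariance. An ANCOVA at each visit with baseline and hospital would also serve. State that the group × visit p-value is not the efficacy test.

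The cost is wording, minor programming and two degrees of freedom for three hospitals. The data and the stratum are already collected, and trial conduct does not change.
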